##### Gut microbiome analysis

Taxonomic profile will be characterised using Kraken2,^63^ and metabolic profile will be characterised through the HUMAnN2 pipeline.^64^ We will calculate α-diversity (within-sample diversity) using the Shannon Index to account for both richness and evenness within the dataset. A sensitivity analysis will be conducted to test the effects of using richness and Pielou’s evenness. For β-diversity (between-sample diversity), we will generate distance matrices using both phylogenetic (weighted and unweighted UniFrac) and non-phylogenetic (Bray-Curtis, Jaccard, Aitchison) indices. These matrices will be used to quantify differences in gut microbiome profiles between cases and controls via permutational multivariate analysis of variance and permutational multivariate analysis of dispersion.^65 66^ For the differential abundance analysis, we will describe differences in the mean abundance of microbial taxa and genes by using analysis of composition of microbiomes.^67^ Associations between phenotypic measures—including dietary, psychological, metabolic and clinical measures—and microbial and dietary diversity will be reported using linear models. Using a random forest machine learning model,^31^ we will regress the relative abundance of microbial taxa against the chronological age of each child at the time of stool sample collection. The predicted microbiota ages of the participating children and adolescents will then be compared with the median microbiota age of chronologically age-matched children and adolescents in the control group to generate microbiota-for-age Z-scores.

## Discussion

In addition to an in-depth study of genetic and environmental factors associated with ARFID, ARIES will form the basis of a national research registry and biobank of childhood ARFID cases and controls. The cohort will provide immediate data and samples to address our baseline scientific aims and enable longitudinal follow-up to plot the course of ARFID and identify predictors of long-term outcome. The ARIES repository will be an invaluable resource for investigators who apply for access to questionnaire data, biological samples and participants who will have agreed to re-contact for research. With linkage to population health and quality registers, ARIES will be a unique resource and will be well-positioned to address essential questions about this pernicious and understudied illness.

We will also use our combined ARIES/PGC-ED GWAS data in cross-disorder analyses to determine how ARFID is best positioned genetically relative to other EDs, other psychiatric conditions, such as depression, anxiety and OCD, and to neurodevelopmental conditions, such as autism and attention deficit/hyperactivity disorder. Our unique inclusion of microbial data will reveal much about the impact of ARFID on the gut microbiota and microbiome and may inform the development of nutrition interventions for ARFID (eg, nutrigenomics, microbiota-directed complementary foods).

Furthermore, we will be able to use the genotyping array data to generate CNV calls. Since rare genetic CNVs play a role in neurodevelopmental conditions,^68^ we may find the same in ARFID. Our ARFID Biobank will also be poised for future exome or genome sequencing. The proposed work provides a rich foundation for decades of study of ARFID.

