#### Hypotheses

Sensory-based food avoidance will be genetically related to autism, low appetite to depression and metabolic factors, and fear-based avoidance to anxiety and OCD. We also expect the genetic associations of ARFID with neurodevelopmental conditions and anxiety to be stronger than the genetic associations of ARFID with other EDs.

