#### Recruitment

Study recruitment began in May 2024, and we anticipate closing recruitment in summer 2025. To ascertain cases, we developed and launched a campaign for information dissemination and recruitment using a variety of different methods, including social media, healthcare centres (eg, ED clinics, child and adolescent psychiatry, adult psychiatry and paediatric services), school healthcare and advocacy organisations for EDs and neurodevelopmental conditions. The Centre for Eating Disorders Innovation (CEDI) Social Media Committee assists in designing a campaign of informational material (print, audio and video) containing education about ARFID and invitations to participate in research. To ensure recruitment of a group of participants who represent ARFID distribution in the population, we include drawings of children and adolescents of different genders, ages, bodies and ancestries. To further increase reach, we recruit community members and influencers to promote ARIES. We focus the first part of our recruitment campaign to ascertain ARFID cases and the second part of our recruitment campaign to ascertain ARFID controls.

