### Case definition

Cases will be participants who screen positive for ARFID on the PARDI-AR-Q or NIAS, report no clinically significant disordered eating behaviours in the last 28 days that could suggest the presence of AN or BN on PEDE-Q and have no lifetime diagnosis of AN or BN. Controls will be participants who screen negative for ARFID on PARDI-AR-Q and NIAS, report no clinically significant disordered eating in the last 28 days suggesting the presence of AN or BN on PEDE-Q, have no lifetime diagnosis of any ED or other psychiatric condition, and who have no first-degree relatives with an ED as reported by the parent. Case participants who will be included in the microbiome substudy will display exceptionally high scores on the PARDI-AR-Q subscale for sensory-based food avoidance (see table 1), and control participants will display exceptionally low scores on all PARDI-AR-Q and NIAS subscales. Table 1 presents detailed inclusion and exclusion criteria for cases and controls included in the main study and in the microbiome substudy.

**Table 1 T1:** Inclusion and exclusion criteria for the main study and the microbiome substudy

	Main study		Microbiome substudy	
	Cases	Controls	Cases	Controls
NIAS	PE>9 **OR** LA>8 **OR** F>9	PE≤9 **AND** LA≤8 **AND** F≤9		PE<5 **AND** LA≤1 **AND** F≤1
	**OR**	**AND**		**AND**
PARDI-AR-Q	A0 met **AND** (A1 **OR** A2 **OR** A3 **OR** A4) met	A0—A4 not met	S>5.5*	S≤1 **AND** LA≤1 **AND** F≤1
	**AND**	**AND**	**AND**	**AND**
EDE-Q	Global score <4 **AND** No vomiting **AND** No laxative use	Global score <4 **AND** No vomiting **AND** No laxative use **AND** <5 binge eating episodes		
	**AND**	**AND**		
Control questions	No lifetime diagnosis of AN or BN	No lifetime diagnosis of any ED **AND** No first degree relative with a lifetime diagnosis of any ED **AND** No current diagnosis of a psychiatric disorder	No antibiotics or probiotics during the last 3 months **AND** Never hormones for gender reassignment **AND** No current inflammatory GI condition	No antibiotics or probiotics during the last 3 months **AND** Never hormones for gender reassignment **AND** No current inflammatory GI condition

* Due to the dominance of sensory-based food avoidance in children with ARFID^69^ and in order to obtain a sufficient sample size for microbiome analyses, we focused our microbiome analysis on those with high scores on S to investigate the association of sensory-based food avoidance with the gut microbiome.

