##### Genetic analysis

We will use the Ricopili software pipeline (Rapid Imputation for Consortias Pipeline, developed by PGC) including modules for preimputation (QC), principal component analysis, imputation and meta-analysis to process hundreds of GWAS data sets rapidly and consistently.^54^

First, we will conduct an independent within-disorder GWAS of the ARIES sample alone and then combine the ARIES sample with additional ARFID samples from the PGC-ED to conduct a GWAS meta-analysis. Post-GWAS analyses will include, among others, the analysis of X chromosome (chrX) variants; secondary GWAS analyses separately on females and males to evaluate the similarity to the results of the primary GWAS; clumping GWAS to convert significant single nucleotide polymorphisms (SNPs) (p<5×10^−8^) into regions; conditional and joint analyses; functional genomic integration; linkage disequilibrium score regression (LDSC) to estimate SNP-based heritabilities^55 56^; the calculation of rare copy number variants (CNVs) and CNV burden; the calculation of polygenic risk scores (PRS) using the p-thresholding method and a summary statistics version of Bayesian multiple regression (SBayesR)^57^; an ARFID presentation analysis examining the association between ARFID PRS and PARDI-AR-Q subscale scores sensory-based food avoidance, lack of interest in food or eating and fear; gene-wise tests of association with ARFID using multimarker analysis of genomic annotation^58^; the investigation of partitioned heritability using stratified LDSC,^59^ and whether genes associated with ARFID are enriched in certain tissues, cell types and pathways.

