We will compare disorder-specific GWAS for ARFID, AN, BN and BED and transdiagnostic behaviours (eg, restriction, binge eating). Analyses will include, among others, the calculation of common variant-based genetic correlations (SNP-r_g_s) for ARFID and selected traits to investigate common genetic variation using GWAS summary statistics; generalised summary data-based Mendelian randomisation to investigate causal relationships between ARFID and selected traits; multitrait-based conditional and joint analysis (GCTA-mtCOJO)^60^ to investigate whether SNP associations for EDs can be traced back to their relationship with correlated traits such as type 2 diabetes, body mass index and depression; the calculation of disorder-specific SNP associations by conducting a case vs case GWAS (eg, ARFID vs BED) and multipolygenic scores^61^ by using the largest available GWAS summary statistics of psychiatric and somatic conditions and traits to predict selected outcomes (ARFID, AN, BN, BED); and genomic structural equation modelling^62^ to investigate the genetic architecture of ARFID compared with other EDs.

Finally, we will analyse whether ARFID is genetically associated with various psychiatric, neurodevelopmental, somatic and other relevant phenotypes by making use of the same methods outlined above. Summary statistics of selected traits are provided by other PGC working groups and the UK Biobank.

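### The ARIES CNV-burden comparison cannot separate an ARFID effect from a comorbid neurodevelopmental effect; report it also by neurodevelopmental status

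*Protocol article*

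**What the plan says.** - **Recruitment.** Case-finding channels include social media, clinics, school healthcare and "advocacy organisations for EDs and neurodevelopmental conditions".
- **Case definition and Table 1.** The diagnostic exclusion for cases is "no lifetime diagnosis of AN or BN", plus current behaviours suggesting either. NDD diagnoses are not restricted. Controls, by contrast, must "have no lifetime diagnosis of any ED or other psychiatric condition". Table 1 gives the psychiatric part of that rule as current rather than lifetime.
- **Hypotheses under Aim 1.** The authors themselves expect more neurodevelopmental conditions in cases than in controls.
- **Genetic analysis.** The post-GWAS list includes "the calculation of rare copy number variants (CNVs) and CNV burden".
- **Data analysis.** Age and sex/gender are the covariates named for all analyses. Separate analysis plans for genotype data are referred to but are not part of the article.
- **Discussion.** The reason given for looking at CNVs is "Since rare genetic CNVs play a role in neurodevelopmental conditions,^68^ we may find the same in ARFID".
- **Assessment battery and Additional data sources.** NDD conditions are recorded by questionnaire and through the National Patient Register (NPR).

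**The concern.** The argument in the Discussion runs from a CNV role in NDD to a possible CNV role in ARFID. To test it, the comparison must be able to show a CNV excess that belongs to ARFID and not simply to children who also have NDD. The eligibility rules work against this. Comorbidity is unrestricted in cases, and one recruitment channel favours it, while controls are selected for the absence of psychiatric diagnoses. If ARFID had no relation to CNVs at all, a case group with a substantial NDD share would still show a higher burden than these controls.

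What is at stake is the interpretation of a positive result. The study's overall aim is an aetiological model of ARFID, and a CNV finding that could be wholly explained by comorbid NDD would not inform that model in the way the Discussion suggests.

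**Working it through.** The article states no CNV frequency, CNV effect size or NDD share among cases, so there is no figure of its own to reproduce. The following is an illustration.

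**Inputs from the article:** 1500 cases and 500 controls (Participants, Objective).

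**Assumed inputs, not in the article:**
- carrier share without NDD, p0 = 1%
- carrier share with NDD, p1 = 2%-6%
- NDD share among cases, f = 20%-50%
- no NDD among controls
- no effect of ARFID itself on carrier status

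**Formulas:**
- Carrier share in cases: pc = f × p1 + (1 − f) × p0
- Apparent odds ratio: OR = [pc/(1 − pc)] / [p0/(1 − p0)]
- Chance of a significant excess in cases: normal-approximation power for two proportions, 1500 v 500, two-sided α = 0.05. With no confounding this chance would be 2.5%.

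**Results:**

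| p1 | f | pc | Apparent OR | Chance of significant excess |
|---|---|---|---|---|
| 2% | 20% | 0.2 × 0.02 + 0.8 × 0.01 = 1.20% | 1.20 | 5% |
| 2% | 50% | 0.5 × 0.02 + 0.5 × 0.01 = 1.50% | 1.51 | 11% |
| 3% | 20% | 0.2 × 0.03 + 0.8 × 0.01 = 1.40% | 1.41 | 8% |
| 6% | 35% | 0.35 × 0.06 + 0.65 × 0.01 = 2.75% | 2.80 | 65% |
| 6% | 50% | 0.5 × 0.06 + 0.5 × 0.01 = 3.50% | 3.59 | 89% |

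The carrier counts show how few events are involved. Controls would be expected to have 500 × 1% = 5 carriers. Cases would have 1500 × 1.20% = 18 to 1500 × 3.50% = 52.5, against 15 with no NDD among them.

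**Sensitivity to the control assumption.** With p0 = 1%-2%, an NDD odds ratio for carrier status of 2-3 and f = 10%-50%, the apparent OR is 1.10-1.99 if controls are free of NDD. It is 1.05-1.81 if 5% of controls have NDD. The distortion shrinks but keeps its direction.

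**After stratification.** If NDD-free cases are compared with NDD-free controls, both have carrier share p0 in this scenario, so the apparent OR is 1.00 by construction.

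**Cost in precision.** With f = 20%-50%, 1500 × 0.8 = 1200 to 1500 × 0.5 = 750 cases remain. At p0 = 1% the OR detectable with 80% power moves from 3.22 with all 1500 cases to 3.30 with 1200 and 3.51 with 750. The loss is modest because the 500 controls are the smaller group for all these values.

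**The case against.** **The article fixes no such interpretation, and a stratified analysis may be in the genotype plan.** Both points stand in part. A reader might infer that a CNV excess will be credited to ARFID. The Discussion says only that such a finding may occur, and no formal hypothesis concerns CNVs. Absence of a stratum from a condensed article is not itself a fault. What remains is that the article does fix unequal eligibility, the recruitment channel and a rationale that together leave the inference unidentified.

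**NDD comorbidity may be part of ARFID rather than a bias.** This stands. If CNVs raise ARFID risk through NDD, removing NDD cases removes real aetiology, and only the excess created by recruitment is ascertainment bias. NDD organisations are one channel among several. This is a reason to report both estimates, not to replace the overall one.

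**Controls may not be NDD-free.** This also stands. The screen refers to psychiatric conditions, while the article often lists neurodevelopmental conditions separately, so the zero share in controls is an assumption.

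Three stronger readings are tempting, and the document does not support them:
- *The common-variant conditioning analysis overlooks autism and ADHD.* Its named traits, "correlated traits such as type 2 diabetes, body mass index and depression", are examples, and the Genetic analysis section goes on to apply the same methods to neurodevelopmental phenotypes.
- *The distortion extends to the whole meta-analysis or to genetic correlations.* Recruitment is described only for ARIES, which supplies 1500 of the 9000 cases in Table 2. The case mix of the other cohorts is not given, and no pooled CNV analysis is explicitly stated.
- *NDD cases should be removed before testing the Aim 4 ranking* ("We also expect the genetic associations of ARFID with neurodevelopmental conditions and anxiety to be stronger than" those with other eating disorders). That would select cases on NDD liability and push the ranking the other way.

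**Conclusion.** The point holds for CNV burden in ARIES. With NDD unrestricted in cases, psychiatric diagnoses screened out of controls, and age and sex/gender as the only named covariates, the planned contrast cannot distinguish an ARFID effect from a comorbid-NDD effect. The direction of the distortion follows from the design, provided that CNVs are more frequent in NDD, which the article itself accepts, and that cases have more NDD than controls, which it expects. Its size is not known. An apparent OR of about 1.2-3.6 with a 5%-89% chance of significance rests entirely on the assumed carrier and NDD shares, and at the low end it would hardly be noticed in 2000 participants. This is an inexpensive improvement to what a positive result can support. It does not invalidate the genetic programme.

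**What to change.** In ARIES, report CNV burden three ways against controls: all cases, cases with an NDD or intellectual-disability diagnosis, and cases without one. Define NDD status from the questionnaires and the NPR together, since the article puts NPR coverage of specialised outpatient care at around 80%, and check controls by the same definition. State in advance that a CNV role in ARFID independent of NDD will be claimed only if it is seen in the NDD-free stratum.

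Recruitment and data collection do not change. The cost is a smaller stratum with wider intervals: 750-1200 of 1500 cases under the assumed shares. The NDD-free estimate also leaves out any CNV effect that acts through NDD, which is why the overall estimate should stay in the report. Undiagnosed NDD among the remaining cases would leave some residual confounding, and this should be acknowledged.
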